Artemisinin-containing combination therapies (ACTs) such as DP are now the standard for the treatment of *Plasmodium falciparum* malaria in both children and adults [6]. A systematic review of the efficacy and safety of ACTs showed that DP is very effective and provides a long duration of post-treatment prophylaxis similar to mefloquine and a longer duration than amodiaquine or lumefantrine-based combinations [6, 7]. Because of its long half-life, piperaquine has great potential for use as the ACT of choice for intermittent treatment and chemoprophylaxis, as was shown in intermittent preventive treatment (IPT) studies in children [8]. We propose dihydroartemisinin-piperaquine as the chemopreventive agent of choice for children with SCA on the continent.

A trial with monthly DP used as IPT in Thai adults showed it to be well-tolerated, safe and highly effective [9]. The most important determinant of protective efficacy was the trough plasma concentration of piperaquine, and this was determined by the dosing frequency. The study suggested that for effective prevention of malaria, DP should at least be given monthly to achieve steady-state concentrations above the minimum inhibitory concentrations and sustained prophylactic levels. Piperaquine is currently only available in the fixed-dose combination with dihydroartemisinin (DHA) as DP. The DHA component, eliminated within a few hours, is not expected to contribute significantly to chemoprevention effects, yet may provide a degree of protection against the development of piperaquine resistance in the population.

Side effects of DP in adults include transient drops in haemoglobin by day 7 (seen with all ACT), headache, weakness, and fever. Its main safety concerns relate to its dose-dependent QT prolongation seen in clinical trials, including our post-discharge chemoprevention of malaria in transfused children (PMC) study [10]. Nevertheless, the side effects of DP are mild and similar to that seen with other anti-malarial drugs [11]. There is also no indication from the data signalling that it is associated with clinically significant arrhythmia [12].

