#### Intervention description {11a}

Participants will be randomly allocated to receive one of two medications: weekly DP + monthly SP placebo or monthly SP + weekly DP placebo.

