#### Other outcomes

##### Safety outcomes

Incidence of serious adverse events (SAEs; grade 3 or 4 adverse events) according to the Common Terminology Criteria for Adverse Events (CTCAE) toxicity tables and coded using MedDRAAdverse events (grade 1 or 2 toxicity) after enrolmentIncidence of serious cardiac adverse events (convulsions or syncope within 48 h after drug intake)Change in QTc length and QTc-prolongation on four-monthly ECG recordings and by the age-dependent cut-off value (in a subset of patients)

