#### Secondary efficacy outcomes

Intention-to-treat analysis shall be followed for analysis of secondary outcomes. For count secondary outcomes, all sick visits, malaria-specific sick visits, all-cause hospitalisations, malaria-specific hospitalisations, serious cardiac adverse events and SCA-related vaso-occlusive events, we shall fit Poisson regression models and compare events between the intervention groups using incidence rate ratios. Negative-binomial regression models will be fitted if there is overdispersion. Model adjusters shall be informed by imbalances in baseline characteristics between the intervention groups. We shall fit a binary logistic model to compare the odds of death between the two intervention groups. Death shall likely be a rare outcome in this study, and often, binary logistic regression models face convergence problems due to the sparse outcome. We shall instead fit models using the firth method, which avoids the convergence challenges of the logistic regression model when the outcome is rare. We shall report odds ratios as measures of association. We shall also test if the change in QTc length from baseline is > 60 ms using a one-sided *t*-test. We will provide a list of individual participant changes in QTc length from baseline. Exploratory quantitative outcomes shall be summarised by the intervention arm using descriptive statistics. Qualitative exploratory outcomes such as user and provider experiences of the intervention, satisfaction with the intervention and treatment preference will be described as text. We shall also present a list of adverse events and document if they were related to the study drug or not.

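### The stated QTc test sets 60 ms as the null value for a mean change and names no DP versus SP contrast, so a non-significant result would say nothing about QTc prolongation

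*Protocol article*

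**What the plan says.** The QTc analysis is in the protocol article, under Secondary efficacy outcomes: "We shall also test if the change in QTc length from baseline is" greater than "60 ms using a one-sided" t-test. The next sentence adds "We will provide a list of individual participant changes in QTc length from baseline". No other QTc analysis is stated. The text does not say whether the test is run in each arm, in both arms pooled, or on the difference between arms, nor which ECG visits enter it.

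The outcome itself is defined under Safety outcomes as "Change in QTc length and QTc-prolongation on four-monthly ECG recordings and by the age-dependent cut-off value (in a subset of patients"). The background section says of DP: "Its main safety concerns relate to its dose-dependent QT prolongation seen in clinical trials". Cardiac safety of cumulative DP dosing is one of the secondary objectives.

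Other outcomes in the same analysis section do get a comparison by arm. For several counts the plan reads: "serious cardiac adverse events and SCA-related vaso-occlusive events, we shall fit Poisson regression models and compare events between the intervention groups". Deaths are compared by odds ratio. The allocation is "weekly DP + monthly SP placebo or monthly SP + weekly DP placebo", so a concurrent randomised control exists.

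**The concern.** A t-test makes a statement about a mean. With 60 ms as the tested value and a one-sided alternative above it, the test can reach significance only if the average change is convincingly more than 60 ms. Many individual children could exceed 60 ms while the mean stays well below it, and the test would stay silent.

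At stake is the one QTc inference the article states, on what it calls DP's main safety concern. A non-significant p-value is close to certain whether DP has no effect on QTc or raises it by 40 ms on average. If reported alone, it could be taken as reassurance that the data do not give. The test also does not address prolongation by the age-dependent cut-off, which the article lists as an outcome, and no DP versus SP estimate of QTc change is specified.

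**Working it through.** The plan gives no sample size, SD or power for QTc, so there is no planned figure to reproduce.

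**Inputs.** From the article: tested value 60 ms, one-sided t-test, significance at 0.05 (stated for efficacy; no separate level is given for QTc), 1:1 allocation, ECGs in a subset. Assumed: n = 25, 50, 100 or 274 children per arm with ECGs (274 being the whole arm in the 548-participant design), SD of individual change 15, 20 or 30 ms, normal changes.

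**Step 1: mean needed for significance.** In one arm the observed mean must exceed 60 + t(0.95; n−1) × SD/√n.
- n = 274, SD 15: 60 + 1.650 × 0.906 = 61.5 ms.
- n = 25, SD 30: 60 + 1.711 × 6 = 70.3 ms.

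**Step 2: chance of significance in one arm.** The statistic is noncentral t with n−1 degrees of freedom and noncentrality (mean − 60)/(SD/√n). The most favourable case tried for a true mean of 50 ms is n = 25, SD 30: noncentrality (50 − 60)/6 = −1.67, probability 0.00055. Every other combination gives less.

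**Step 3: the other readings.**
- On the DP minus SP difference, noncentrality is (difference − 60)/(SD × √(2/n)). For a 50 ms difference, n = 25 per arm, SD 30: −10/8.49 = −1.18 with 48 degrees of freedom, probability 0.0025, again the largest in the range.
- Pooled, with equal numbers per arm and no change on SP, the pooled mean is half the DP mean. The DP mean would have to exceed 120 ms before the pooled mean passed 60 ms.

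**Step 4: children above 60 ms meanwhile.** The share is 1 − Φ((60 − mean)/SD). For a mean of 30 and SD 20: 1 − Φ(1.5) = 6.7%. In the last column the first column is read as the DP minus SP difference.

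| True mean rise | Children above 60 ms (SD 15 / 20 / 30) | Largest chance of significance, one arm | Largest chance, on the difference |
|---|---|---|---|
| 30 ms | 2.3% / 6.7% / 15.9% | below 0.000001 | below 0.000001 |
| 40 ms | 9.1% / 15.9% / 25.2% | below 0.000001 | 0.00004 |
| 50 ms | 25.2% / 30.9% / 36.9% | 0.00055 | 0.0025 |
| 60 ms | 50% / 50% / 50% | 0.05 | 0.05 |

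At a true mean of exactly 60 ms, half the children are above 60 ms and the test is significant one time in twenty.

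**Step 5: the reversed direction.** If the intention were to show a mean below 60 ms, a true mean rise of 40 ms would pass with probability 94% at n = 25, SD 30 (noncentrality 20/6 = 3.33) and above 99% in every other combination. That version does not discriminate either.

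**Step 6: a between-arm comparison against zero.** Two-sided 0.05, two-sample t-test of QTc change:
- True difference 20 ms: power 93% at 25 per arm, SD 20; 64% at 25 per arm, SD 30, the worst case tried.
- True difference 10 ms, SD 20: 41%, 70% and 94% at 25, 50 and 100 per arm.
- Half-width of the 95% CI at SD 20: 2.011 × 20 × √(2/25) = 11.4 ms at 25 per arm; 1.972 × 20 × √(2/100) = 5.6 ms at 100 per arm.

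**The case against.** The strongest reply is that the t-test is only one part of the cardiac safety plan. Serious cardiac adverse events (convulsions or syncope within 48 h of drug intake) are compared by rate ratio. Every measured child's QTc change is listed, so any change above 60 ms would be visible. Prolongation by the age-dependent cut-off is a defined outcome, and the data safety and monitoring board reviews safety results and may ask for unblinded analyses. QTc is listed among the other outcomes, in a subset only, and an unseen analysis plan may add detail.

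Much of this stands, and it rules out several stronger readings that a reader might infer:
- That the test ignores the control arm or is within-group. The article names no contrast, so neither is established. Steps 2 and 3 show that the weakness does not depend on the reading.
- That the four-monthly repeat ECGs go unused. The article does not say which visits enter the test, and visit handling is commonly left to an analysis plan.
- That the cardiac safety objective cannot be answered at all. The event comparison and the listing contribute to it.
- That the trial will declare QTc safe on a non-significant result. No such decision rule is attached to the test.

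The mean rises and SDs used above are illustrations; the documents give no expected QTc shift.

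The objection does not rescue the test. The clinical events are not QTc measurements, a listing is not a comparison, and the 60 ms null is a stated rule rather than a missing detail.

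**Conclusion.** The concern holds in this form: the only QTc inference stated in the article tests a mean against 60 ms and names no DP versus SP contrast. It has practically no chance of significance unless the mean rise (or the between-arm difference, if that is what is tested) itself exceeds 60 ms. At a true value of 50 ms the chance is at most about 0.0005 in one arm and about 0.0025 on the difference. A non-significant result would therefore carry no information about QTc prolongation.

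The figures rest on an assumed SD of 15 to 30 ms, 25 to 274 children per arm, normal changes and a 0.05 level. The conclusion is the same throughout that range. This is a should-fix rather than a must-fix: it concerns a safety outcome in a subset, and the primary efficacy conclusion is unaffected.

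**What to change.** Delete the one-sided t-test against 60 ms and put in its place:
1. The DP minus SP difference in QTc change from baseline with a 95% CI, adjusted for baseline QTc. A mixed model over the four-monthly ECGs is one suitable way; analysis of covariance at a named visit is a simpler one.
2. By arm, the number and proportion of children with a change above 60 ms, and likewise above the age-dependent cut-off, each with the risk difference and its CI.
3. The individual listing, kept as planned.

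State the size of the ECG subset and its split by arm, since ECGs need separate consent and neither figure is given.

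The cost is revised wording in the protocol and analysis plan, settled before unblinding. It needs no ECGs beyond those planned, provided that the subset includes children from both arms; nothing in the article limits it to one. The downside is precision. If the subset is small, the interval will be wide (about ±11 ms at 25 per arm with SD 20) and the proportions will rest on few children. The interval would at least show that uncertainty, which the present test does not.

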### Interim analyses {21b}

Only one interim efficacy analysis is planned to assess the primary outcome when the study reaches approximately 50% follow-up time, i.e. about 412 person-years follow-up per study arm time accumulated across all study sites or at least half of the estimated number of events (62 out of an anticipated 124 events across both arms). This information will be used to determine if the study should continue as planned, proceed with modifications or be terminated. The Haybittle–Peto boundary will be used as a stopping rule, which states that a trial could be stopped early if an interim analysis shows a probability ≤ 0.001 that a difference as extreme or more between the treatments is found, given that the null hypothesis is true.

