### Sample size {14}

The minimum incidence rate of clinical malaria in SCA patients receiving monthly SP is estimated at 0.2 events per year. Assuming an effect size of 50% if DP is used (i.e. a 50% reduction in the rate as in Bigira et al. [27] that is, a hypothesised incidence rate of 0.1 events per person per year in the DP group), at a power of 0.9 and 0.05 level of significance, we will need 438 individuals to be followed up for 18 months. Allowing for 20% losses to follow-up, we shall need 548 participants (274 in each group) to be followed for an average of 18 months, equivalent to 9864 person months, or 824 participants for an average follow-up of 12 months, equivalent to 9888 person-months.

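### The person-time trigger for the interim analysis, 412 person-years per arm, is all of the planned follow-up and not half of it; half is about 206 per arm, or 412 across both arms.

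*Protocol article*

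**What the plan says.** **Interim analyses {21b}.** One efficacy look at the primary outcome is planned, at roughly half of the follow-up time. The section glosses this as "about 412 person-years follow-up per study arm" and adds, joined by *or*, a count of at least half the expected events: "62 out of an anticipated 124 events across both arms". The look uses a Haybittle–Peto boundary (p ≤ 0.001) and informs whether the trial continues, is modified or stops.

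**Sample size {14}.** The rates are stated as "The minimum incidence rate of clinical malaria in SCA patients receiving monthly SP is estimated at 0.2 events per year" and "a hypothesised incidence rate of 0.1 events per person per year in the DP group". The size is given as "at a power of 0.9 and 0.05 level of significance, we will need 438 individuals to be followed up for 18 months". After the allowance for losses, the 18-month option is 548 children, "to be followed for an average of 18 months, equivalent to 9864 person months". The 12-month option is 824 children, "equivalent to 9888 person-months". Both person-month totals cover the two arms together.

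**Trial design {8}.** Allocation is 1:1.

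**Plans for assessment and collection of outcomes {18a}.** Two-monthly visits continue until the required person-months have been observed.

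**The concern.** A person-time figure offered as the half-way mark should be half of the planned total. Here the per-arm figure equals the whole per-arm plan. The event count in the same sentence is a true half, so the sentence offers two versions of the half-way point that are a factor of two apart.

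At stake is the timing of the only planned efficacy look. Read on the person-time figure alone, the look coincides with the planned end of follow-up, and a stopping boundary then has nothing left to stop. At a correctly timed half-way look, the chance of crossing the boundary under the planning assumptions is about 24% (shown under the working), so a properly placed look has real use. Whoever monitors accrual also has to know which number to watch.

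**Working it through.** **Inputs.** From Sample size {14}: rates 0.2 (SP) and 0.1 (DP) per person-year, power 0.9, significance level 0.05, 20% losses, 548 × 18 months or 824 × 12 months. From Trial design {8}: 1:1 allocation. From Interim analyses {21b}: 412 person-years per arm, 62 of 124 events. The protocol does not state whether the significance level is one- or two-sided; two-sided reproduces its numbers.

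**1. The plan's own sample size.** For two Poisson rates with a Wald test on the log rate ratio:

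person-years per arm = (1.960 + 1.282)² × (1/0.2 + 1/0.1) / (ln 0.5)² = 328.05

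328.05 / 1.5 years = 218.7, rounded up to 219 per arm, or **438** in total (matches). 438 / 0.8 = 547.5, rounded up to **548** (matches). The problem is therefore confined to the interim trigger.

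**2. Planned follow-up per arm.**

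| Option | Person-months, both arms | Person-years, both arms | Person-years per arm |
|---|---|---|---|
| 548 × 18 months | 9864 | 9864/12 = 822 | 411 |
| 824 × 12 months | 9888 | 9888/12 = 824 | 412 |

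**3. Fraction represented by the stated trigger.** 412/411 = 100.2% and 412/412 = 100.0%. A true half is 205.5 or 206 person-years per arm, which is 411 or 412 across both arms.

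**4. Check against the event trigger.** Expected events = 0.2 × T + 0.1 × T, with T in person-years per arm.

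- T = 412: 82.4 + 41.2 = **123.6**, the protocol's full anticipated 124.
- T = 206: 41.2 + 20.6 = **61.8**, the protocol's 62.

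The protocol's own event counts therefore place 412 per arm at the end of planned follow-up and 206 per arm at the middle.

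**5. Which trigger fires first.** The person-time trigger comes first only if fewer than 62 events have occurred by 824 person-years in total. Treating total events as Poisson:

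- planned rates, mean 123.6: P(≤ 61) ≈ 3 × 10⁻¹⁰
- rates 25% below plan, mean 92.7: P(≤ 61) ≈ 0.0003
- rates 50% below plan, mean 61.8: P(≤ 61) ≈ 0.49

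The break-even is an average rate of 62/824 ≈ 0.075 per person-year, against the planned (0.2 + 0.1)/2 = 0.15.

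**6. Value of a correctly timed look.** At 206 person-years per arm, SE(log rate ratio) = √((5 + 10)/206) = 0.270. The expected Z is ln 2 / 0.270 = 2.57, and P(Z > 3.29) ≈ 0.235. This describes the look as intended and is not a measure of what the wrong figure costs.

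**The case against.** The strongest reply is that the slip hardly ever decides anything. The triggers are alternatives, and on the natural reading the first one met brings on the look. At the planning rates that is the 62-event trigger, with near certainty. The Sample size section also calls the control rate a minimum, so the planners expected events at this pace or faster. The intent is plain too: the verbal description of half the follow-up, the verbal description of half the events and the 62-of-124 count all agree, and only the per-arm label is out of line. All of this stands, and it limits the consequence. It does not make the figure right. The sentence distinguishes per-arm from both-arm quantities itself, and nothing in the protocol plans the 1648 person-years (4 × 412) that would make 412 per arm a half-way point.

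Three stronger readings are tempting, and the document does not support them.

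- *The interim look is disabled.* A reader might infer this from the person-time figure alone, but the event trigger is correct and remains available.
- *The trigger might never be reached.* If children lost to follow-up contributed no time, about 329 person-years per arm would accrue (438 × 1.5 / 2 = 328.5). However, the Assessment of efficacy section censors them at death, withdrawal or last visit, so their time counts, and the outcome-collection section continues visits until the required person-months are reached. On that rule 412 per arm is reached, at the end.
- *The final inference is damaged.* Sample size, power and the final analysis do not depend on this figure, and a look at p ≤ 0.001 spends negligible alpha whenever it occurs.

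**Conclusion.** The figure is wrong as written. The stated person-time trigger is 100% of planned follow-up, and half is about 206 person-years per arm. The discrepancy is a factor of two between triggers that the protocol presents as equivalent. The likely explanation is that a correct both-arm half-way total was labelled as a per-arm figure.

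The practical effect is limited. Under the planning rates the event trigger delivers the look at about half-way. The person-time figure would set the timing only if events ran at about half the planned rate or less, or if it were taken as the operative clock. In either case the look would come at the planned end of follow-up, with no scope for early stopping.

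The conclusion that 412 per arm is the whole plan rests only on the protocol's person-months and 1:1 allocation. The statement about which trigger fires first rests further on the planning rates, Poisson event totals and the reading that whichever trigger is met first applies.

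**What to change.** In Interim analyses {21b}, replace the person-time figure with about 412 person-years accumulated across both arms (about 206 per study arm). Leave the event trigger unchanged, carry the corrected figure into any analysis plan or DSMB document that repeats it, and notify the DSMB.

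Optionally, add a clause saying which trigger governs if the two disagree. Two alternative triggers are legitimate once the figure is right, so this is a matter of preference.

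The cost is a one-line correction and a note to the DSMB. It needs no further participants or data and does not change the sample size, the boundary or the final analysis.

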### Methods for additional analyses (e.g. subgroup analyses) {20b}

#### Subgroup analyses

For sub-analysis, we will use stratified analysis to assess to what extent the effect of the intervention on the primary outcome is influenced by site, demographic (e.g. age, and socio-economic status) or clinical parameters, malaria transmission variables (malaria transmission intensity, residence (urban/rural), season, insecticide-treated nets use, site), time of assessment and potential intervention modifiers.

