**Methods:**

This will be a randomised, double-blind, parallel-group superiority trial of weekly single-day courses of DP compared to monthly single-day courses of SP in children with SCA. The study will be conducted in eastern (Uganda) and southern (Malawi) Africa using randomisation stratified by body weight and study centre. Participants will be randomised using an allocation of 1:1 to DP or SP. We will investigate the efficacy, safety, acceptability and uptake and cost-effectiveness of malaria chemoprevention with weekly courses of DP vs monthly SP in 548 to 824 children with SCA followed up for 12–18 months. We will also assess toxicity from cumulative DP dosing and the development of resistance. Participant recruitment commenced on 30 April 2021; follow-up is ongoing.

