### Secondary objectives

Assess the feasibility and stakeholder perceptions on the uptake (acceptability) and the potential for future roll-out of weekly DP vs monthly SPDetermine the safety of cumulative dosing of DP, especially on cardiac functionMonitor the development of malaria parasite resistance to DP in clinical isolates over timeAssess patients’ health-related quality of life, cost-effectiveness, equity and economic implications of using weekly courses of DP vs monthly courses of SP as chemoprevention in SCAConduct policy advocacy to engage key stakeholders on policy decisions on using weekly courses of DP or monthly courses of SP for the chemoprevention of malaria in SCA

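### Cardiac safety of cumulative DP dosing is a stated objective, but no stated safety analysis uses the serial ECGs to show whether the DP-versus-SP QTc difference plateaus or grows

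*Protocol article*

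**What the plan says.** All references are to the protocol article.

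- **Objective.** Secondary objectives include determining "the safety of cumulative dosing of DP, especially on cardiac" function. The abstract's Methods repeats this: "We will also assess toxicity from cumulative DP dosing and the development of resistance".
- **Data.** Safety outcomes include change in "QTc length and QTc-prolongation on four-monthly ECG recordings", in a subset of patients, and the incidence of serious cardiac adverse events, defined as convulsions or syncope within 48 h of drug intake.
- **Analysis of QTc.** Under Secondary efficacy outcomes: "We shall also test if the change in QTc length from baseline is > 60 ms using a one-sided *t*-test". A list of individual changes from baseline is also promised.
- **Analysis of cardiac events.** The same section names serious cardiac adverse events among the count outcomes, for which "we shall fit Poisson regression models and compare events between the intervention groups using incidence rate ratios", with negative-binomial models if there is overdispersion.
- **Analysis by time.** Subgroup analyses states: "we will use stratified analysis to assess to what extent the effect of the intervention on the primary outcome is influenced by site", and goes on to list other possible modifiers. Time of assessment appears once, in that list, as a possible modifier of the effect on the primary outcome. The primary outcome is clinical malaria.

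**The concern.** A question about cumulative dosing has an exposure axis: as weekly doses continue over 12 to 18 months, does the QTc difference between DP and sulphadoxine-pyrimethamine (SP) stay where it was at the first ECG, or does it increase? The background section names dose-dependent QT prolongation as the main safety concern with DP, and a repeated ECG schedule is what one needs to answer this. Yet no stated safety analysis contains visit, time on treatment or number of doses. If the plan is followed as written, the trial collects the data for the objective without a test or estimate that addresses it, and a drift would be noticed only by someone reading the listing.

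This is separate from the choice of 60 ms as the null value. A plain comparison of mean QTc change between DP and SP, without visit in the model, would leave the same gap.

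**Working it through.** **1. The plan's own figures.** The article gives no sample size, variance or power for the ECG subset, so there is nothing to reproduce on this point. The calculations below are illustrations, and their assumptions are labelled.

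**2. Does the stated QTc test respond to a drift?** It compares a mean change with 60 ms, one-sided; I assume the 5% level. The probability of rejection is approximately Φ[(m − 60)/(SD/√n) − 1.645]. The assumptions are n from 30 to 100 and SD from 15 to 25 ms. Take the case most favourable to rejection in that range: m = 30, n = 30, SD = 25. Then (30 − 60)/(25/√30) = −6.57, less 1.645 gives −8.22, and the probability is effectively 0. It is also effectively 0 at m = 10 and m = 15. A mean change that rose from 10 to 30 ms would give the same non-significant result at every visit. No arm contrast is named either, so the test does not estimate a DP minus SP difference.

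**3. Does one rate ratio for cardiac events respond to a rising effect?** The larger design option is 824 participants followed for an average of 12 months, so 824/2 = 412 person-years per arm. Split this into three equal four-month periods and assume an SP rate of 0.02 per year, which is 0.02 × 412/3 = 2.75 SP events per period.

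| Rate ratio by period | DP events by period | Overall rate ratio |
|---|---|---|
| 2, 2, 2 | 5.5, 5.5, 5.5 | 16.5/8.24 = 2.0 |
| 1, 2, 3 | 2.7, 5.5, 8.2 | 16.5/8.24 = 2.0 |

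The single ratio is the same in both cases.

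**4. Would a time-by-arm test on cardiac events help?** Compare period 3 with period 1 in the rising case. With b SP events per period, the SE of the log ratio of rate ratios is √(1/b + 1/b + 1/b + 1/(3b)), and power is Φ(ln 3/SE − 1.96).

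| Assumed SP rate per year | b | SE | Power |
|---|---|---|---|
| 0.01 | 1.37 | 1.56 | 10% |
| 0.02 | 2.75 | 1.10 | 17% |
| 0.05 | 6.87 | 0.70 | 35% |

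This is too little for a formal test.

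**5. Would an arm-by-visit trend in QTc help?** Four-monthly ECGs give visits at months 4, 8 and 12, and also month 16 if follow-up is 18 months. With a common within-child correlation of 0.5, the SE of the between-arm difference in slope per visit step is SD × √(0.5/SS) × √(2/n). SS is the sum of squared centred visit numbers: 5 for four visits, 2 for three. Power for a drift of 5 ms per step is Φ(5/SE − 1.96). With SD = 20 ms:

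| n per arm | ECGs | SE (ms) | Power |
|---|---|---|---|
| 50 | 4 | 20 × √(0.5/5) × √(2/50) = 1.26 | 98% |
| 50 | 3 | 20 × √(0.5/2) × √(2/50) = 2.00 | 71% |
| 30 | 4 | 20 × √(0.5/5) × √(2/30) = 1.63 | 87% |
| 30 | 3 | 20 × √(0.5/2) × √(2/30) = 2.58 | 49% |

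The SE is proportional to the SD. Over an SD of 15 to 25 ms, power in the best row runs from above 99% down to 89% (SE 0.95 to 1.58), and in the weakest row from 73% down to 34% (SE 1.94 to 3.23).

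**The case against.** The strongest objection is that this is detail for the statistical analysis plan. Only a condensed article is shown, and visit terms for safety outcomes are routine content of an analysis plan. That would settle the matter if the article were silent. It is not: it fixes a particular test for QTc and a particular model for cardiac events, and neither fits the objective. A fuller plan may already add a by-visit analysis, and nothing in the article forbids one.

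A second objection is that cumulative dosing may simply mean many repeated doses, in which case a comparison over the whole period is an answer. That reading is possible, and the pooled event rate ratio serves it. The QTc test does not, because it names no comparison between arms. The article also reports modelling in which steady-state concentrations are reached within a month, which makes a plateau plausible. That is a reason to check for one, and the drift used above is an illustration, not a prediction.

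Three stronger readings are tempting, and the document does not support them:

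- **That QTc is averaged over follow-up.** The article does not say so. The outcome is defined on serial recordings, and the test could be run at any visit. The fault is that no visit is named, so no percentage by which the plan understates a late effect can be derived.
- **That a growing effect could not be detected at all.** The data are collected, and the individual listing might show a drift.
- **That the subgroup section is itself wrong.** Limiting it to the primary outcome is ordinary. It matters here only because it is the one place where time enters an analysis.

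**Conclusion.** The point holds as a mismatch between a stated objective and the stated analyses. The four-monthly ECGs can address cumulative cardiac safety, but neither the QTc test nor the cardiac-event rate ratio draws on their serial structure. The t-test is uninformative for mean changes of 10 to 30 ms under every n and SD assumed, and a single rate ratio is the same for a constant and a rising effect. The gap lies chiefly between Secondary objectives and Secondary efficacy outcomes.

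The power figures for the proposed trend test, about 49% to 98% at an SD of 20 ms, rest on an assumed SD, correlation, drift and subset size, none of which the article gives. They show that the analysis could be worthwhile with a modest subset; they do not predict its performance in this trial. This should be corrected, but it does not touch the primary efficacy result.

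**What to change.** In Secondary efficacy outcomes, and in the analysis plan, specify one mixed model for all post-baseline four-monthly QTc values, with arm, visit, arm-by-visit interaction, baseline QTc, site and weight band, and a random effect for child. Report the DP minus SP difference with its confidence interval at each visit, and the linear trend in that difference. Keep the individual listing and show the visit in it.

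Present serious cardiac events by arm and time since first dose, with the person-time in each window, as a descriptive table only. The overall rate ratio stays as the between-arm comparison.

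The cost is a paragraph of wording and a little more analysis; no new data and no change to treatment are needed. Intervals will be wide at the later visits, where fewer children contribute ECGs.
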